**Methods/design:**

This study is a single-blinded, multicenter, randomized controlled trial. Eighty individuals with MCI will be recruited and randomly assigned to cognitive training (COG), physical exercise training (PE), sequential training (SEQ), and dual-task training (DUAL) groups. The intervention programs will be 90 min/day, 2–3 days/week, for a total of 36 training sessions. The participants in the SEQ group will first perform 45 min of physical exercise followed by 45 min of cognitive training, whereas those in the DUAL group will perform physical exercise and cognitive training simultaneously. Participants will be assessed at baseline, after the intervention, and at 6-month follow-up. The primary cognitive outcome tests will include the Montreal Cognitive Assessment and the color-naming Stroop test. Other outcomes will include assessments that evaluate the cognitive, physical, and daily functions of older adults with MCI.

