In dual-task training, physical exercise and cognitive tasks are performed simultaneously. Dual tasking is one executive function that is especially important for ADLs. Recent studies revealed strong correlations between performance of ADLs and executive function in older adults [25]. Using functional near-infrared spectroscopy, Doi et al. found that increased prefrontal activation during dual tasking was correlated with executive functions in older adults with MCI [26]. Imaging studies in cognitively intact young and old adults also showed that behavioral improvement after dual-task training was associated with changes in prefrontal activation [27, 28]. The evidence from these studies suggests that an intervention using dual-task training could be a promising approach for individuals with MCI.

Behavioral and neurophysiologic evidence suggests that combining physical exercise and cognitive training sequentially or simultaneously has benefits on cognitive functions. However, strong evidence is lacking regarding which combination approach is more feasible, acceptable, and advantageous for older adults with MCI. This proposed randomized controlled trial is designed to address three specific aims: (1) to determine whether combined therapy, sequentially or simultaneously, is a feasible approach to train older adults with MCI, (2) to determine whether combined therapy can induce superior treatment outcomes compared with a single mode of intervention, and (3) to compare which combination approach – sequential or simultaneous – is more advantageous for improving cognitive functions, physical fitness, ADLs, and quality of life in adults with MCI.

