### Sample size estimation

No published study to date has compared the treatment effects of cognitive training, physical exercise training, sequential training, and dual-task training in older adults with MCI. Therefore, we estimated the sample size for the current study from the studies that compared sequential training or dual-task training with control intervention(s) in older adults with cognitive complaints [15–17]. Because our primary outcomes will include global cognitive function and executive function, we calculated the sample sizes on the outcomes that involve these cognitive aspects. Kounti et al. [16] found significant benefits of dual-task training on global cognitive function, as measured by the Mini-Mental State Examination (MMSE), in participants with MCI. Compared with the control intervention, the calculated effect size (Cohen’s *d*) was 0.63 for dual-task training [16]. Using G*Power software [30] with a power of 0.80 and a two-sided type I error of 0.05, the calculated total sample size for the current study will be 20 participants (i.e., 5 participants in each group). The study conducted by Suzuki et al. showed that compared with the control group, the multicomponent dual-task training group had greater improvement in MMSE after intervention [17]. Based on the calculated effect size for the MMSE (Cohen’s *d* = 0.45), we estimated the sample size for the current study will be 12 participants in each group. Barnes et al. investigated the treatment effects of a sequential combination of physical exercise and mental activity training and found significant benefits on the Useful Field of View (UFoV), a measure of executive function, in older adults with cognitive complaints [15]. We used the calculated effect size for the UFoV from Barnes’ study (Cohen’s *d* = 0.21) [15] to estimate a sample size of 32 participants in each group.

Similar to the study design conducted by Barnes et al. [15], we employ the active control groups (i.e., COG and PE groups) instead of a no-treatment or passive control group. On the other hand, the primary outcome measures used in the current study are closer to those used by Kounti et al. [16] and Suzuki et al. [17]. Hence, a mean value from the estimated sample sizes of the three studies was calculated, and we anticipated that recruiting 16 participants for each group should be sufficient for this proposed study.

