#### Primary outcome measures

The MoCA will be used to assess general cognitive function. The MoCA examines visuospatial processing, naming, verbal fluency, abstract concept, short-term memory, digit forward and backward span, counting, and orientation. The total score for the MoCA is 30, with a higher number indicating a more intact cognitive function. The MoCA has been shown to be a valid and promising tool to detect MCI and early Alzheimer’s disease [37].

The color-naming Stroop test will be used to assess the abilities of inhibition, set-shifting, and selective attention [19]. The participants will be tested under congruent and incongruent conditions. In the congruent condition, the ink color of a word is consistent with the written color name; however, the ink color differs from the written color name under the incongruent condition. The participants will be required to read out the ink color of the word (but not the word itself) as accurately and as soon as possible. The time to complete the task will be calculated for each condition [38, 39].

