### Data analysis

We will use analysis of variance (ANOVA) and χ^2^ to analyze differences in baseline characteristics and baseline outcome measures among the groups. Any differences among the groups in the baseline sociodemographic variables will become covariates in the subsequent statistical analysis. Repeated measures ANOVA will be used to determine the intervention effects for the four groups. A significant statistical level will be set at 0.05 for all comparisons. Besides *p* values, effect size η^2^ will also be calculated to determine the group difference for each outcome measure. An η^2^ greater than 0.138 is considered to be a large effect, an η^2^ between 0.138 and 0.059 is a moderate effect, and an η^2^ between 0.01 and 0.059 is a small effect [58]. Intention-to-treat will be used for missing data. Data analysis will be performed with PASW Statistics 18.0 software (IBM Corp., Armonk, NY, USA).

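### The four-group ANOVA does not test the two comparisons named in aims 2 and 3, and reading every comparison at 0.05 leaves the two primary tests with a false-positive chance above 5%

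*Protocol article*

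**What the plan says.** The Background section gives aim 2 as "to determine whether combined therapy can induce superior treatment outcomes compared with a single mode of intervention" and aim 3 as "to compare which combination approach – sequential or simultaneous – is more advantageous". The Data analysis section names one method for the effects: "Repeated measures ANOVA will be used to determine the intervention effects for the four groups". It then sets the level: "A significant statistical level will be set at 0.05 for all comparisons". It adds that eta-squared "will also be calculated to determine the group difference for each outcome measure", with fixed bands for small, moderate and large.

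The abstract names two primary tests: "The primary cognitive outcome tests will include the Montreal Cognitive Assessment and the color-naming Stroop test". For the Stroop test, the Primary outcome measures section says: "The time to complete the task will be calculated for each condition", so it yields a congruent and an incongruent time. Outcomes are assessed at pretest, at posttest and 6 months after treatment. The Sample size estimation section works "with a power of 0.80 and a two-sided type I error of 0.05", undivided.

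**The concern.** Each of aims 2 and 3 is a one-degree-of-freedom question. The stated test asks whether any of the four arms differ. It can be significant for a reason that neither aim covers, it gives no direction, and it spreads its power over contrasts that nobody asked about. A significant result would still leave both questions open, and the next step would be comparisons between arms, each read at 0.05 on two primary outcomes. At stake are the power for the trial's main comparison and the error rate behind any claim that combined training, or one form of it, is better.

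**Working it through.** **The plan's own size.** (5 + 12 + 32)/3 = 16.33, taken as 16 per arm. With 20% dropout, 16/0.8 = 20 per arm, and 4 × 20 = 80. This reproduces. The checks below use n = 16 completers per arm, 64 in all. The SD is set to 1.

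**1. What the omnibus F responds to.** At one visit, λ = n × Σ(μ_i − mean)², with 3 and 60 df.
- Let COG be 0.5 SD below and PE 0.5 SD above a common SEQ and DUAL mean. Then combined minus single is zero and DUAL minus SEQ is zero.
- λ = 16 × (0.25 + 0.25) = 8. The chance of significance is 62%.

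**2. Power for aim 2.** Let both combined arms exceed both single arms by 0.71 SD.
- One visit: λ = 16 × 4 × 0.355² = 8.07. The omnibus F (3, 60 df) has 63% power and the contrast (1, 60 df) has 80%.
- Group-by-time interaction over three visits. Assumptions not in the document: the effect is equal at both later visits, and visits correlate 0.6. The centred time pattern (−2/3, 1/3, 1/3) has sum of squares 2/3, so λ = 8.07 × (2/3)/(1 − 0.6) = 13.44. The interaction F (6, 120 df) has about 77% power and the matching single contrast (1, 120 df) about 95%. That contrast averages the two later visits.

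**3. False-positive chance when nothing differs, two primary tests.**
- One omnibus test per outcome: 1 − 0.95² = 9.75% if independent. Simulation gives 8.3% to 9.9% for outcome correlations from 0.7 to 0.
- Pairs tested only after a significant F: about 5% per outcome and 8% to 10% over the two.
- The five pairs implied by the aims (SEQ and DUAL each against COG and PE, plus SEQ against DUAL), each at 0.05: 17.8% for one outcome and 28% to 33% for two. At correlations of 0.3 to 0.5 it is about 31%.
- One planned contrast per aim on two outcomes, each at 0.05: 15% to 19% (1 − 0.95⁴ = 18.5% if independent).
- If both Stroop times count as primary, which the text allows but does not state, three omnibus tests give 1 − 0.95³ = 14.3% if independent.

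**4. Eta-squared when nothing differs.** Between groups, with 64 completers, the expectation is 3/63 = 0.048, already inside the small band. The chance of exceeding 0.059, the lower limit of the moderate band, is about 30% (28% for the interaction).

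**5. Cost of Holm over four tests.** The strictest step is 0.05/4 = 0.0125. The SD of the estimate is √(1/16) for combined minus single and √(2/16) for DUAL minus SEQ, with 60 df. Differences detectable with 80% power at one visit, without baseline adjustment:

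| Contrast | at 0.05 | at 0.0125 |
|---|---|---|
| Combined v single | 0.71 SD | 0.86 SD |
| SEQ v DUAL | 1.01 SD | 1.21 SD |

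**The case against.** The strongest reply is that this is a condensed article and the analysis plan is not shown. Contrasts, the primary visit, the Stroop score and a multiplicity procedure are commonly left to that plan, and 0.05 for all comparisons could mean adjusted p-values read against 0.05. This stands in part: the absence of those details would be no finding. The point rests instead on what the article fixes, a four-group test as the method for intervention effects and one undivided level for every comparison. The ordinary reading of that level is no adjustment, and nothing in the article qualifies it.

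A reader might go further and infer that a false claim of advantage is more likely than not. The document does not support that. A figure near 60% needs five pairs × three scores × two visits, 30 tests with no gate, and the article states no such family. It also counts differences in both directions. Within that family, a significant advantage of combined over single training arises in about 31% of null trials, and gating by the F brings the any-difference rate down to about 22%.

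Two further objections stand. The 63% against 80% is a one-visit comparison and not the interaction test, so both settings are shown. A pooled contrast has its own weakness: a gain of 1.42 SD in DUAL alone gives a pooled difference of 1.42/2 = 0.71 SD and hence 80% power, and a harm in SEQ could cancel a gain in DUAL. Aim 2 therefore also needs the arm-by-arm estimates.

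The eta-squared point is secondary. The bands are reported in addition to p-values, and nothing says that a label alone supports a claim.

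**Conclusion.** The concern holds in a limited form. The stated omnibus test answers neither aim 2 nor aim 3. Against a direct contrast it gives up about 17 points of power for aim 2 at one visit (63% v 80%), or about 18 points for a sustained effect (77% v 95%). The false-positive chance over the two primary tests is about 9% for omnibus tests or F-gated pairs, and about 31% if the five aim-relevant pairs are each read at 0.05.

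These figures assume 16 completers per arm, equal variances and normal outcomes. The error rates assume no difference among any arms. The 95% and 77% also depend on the assumed visit correlation of 0.6 and a sustained effect. If success required both primary tests to be significant, no adjustment across outcomes would be needed, but the article states no such rule. This should be fixed. It does not invalidate the design.

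**What to change.** From the same repeated-measures model, pre-specify two contrasts: (SEQ + DUAL)/2 − (COG + PE)/2 for aim 2, and DUAL − SEQ for aim 3. Name one primary visit and one primary Stroop score. Posttest and incongruent time are an example; the choice is the sponsor's. Apply Holm's procedure to the four primary tests (two outcomes × two contrasts).

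Report each combined arm against each single arm, and the secondary outcomes, as estimates with 95% confidence intervals. Give contrast mean differences with intervals alongside eta-squared, and note that eta-squared averages about 0.048 under no effect with 64 completers.

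The change is to the analysis text only. The Trial status section reports 39 of 80 recruited, so it can still be fixed before any comparison of arms. The price is the stricter threshold: 0.71 to 0.86 SD for combined versus single, and 1.01 to 1.21 SD for SEQ versus DUAL, at the strictest Holm step. Both exceed the planning effects of 0.21 to 0.63 even before correction. Use of the pretest score in the model would lower these figures by an amount that depends on its correlation with posttest, which the article does not give.

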The dropout rate in our pilot trial was approximately 20 % during the intervention period; hence, we plan to recruit 20 participants for each group resulting in a total sample size of 80 patients for four groups.

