### Study design and procedures

This proposed study is a randomized controlled trial with pretest, posttest, and 6-month follow-up assessments (Fig. 1). The study protocol is approved by the Chang Gung University Institutional Review Board. Intervention therapists will screen for potential participants and obtain signed informed consents from the eligible individuals before they participate in the study. The enrolled participants will be randomly assigned into the COG, PE, SEQ, or DUAL group with the allocation ratio of 1:1:1:1 [31]. Random tables based on the type of recruitment site (day care centers versus nursing homes versus community) will be generated by an independent research assistant using the web-based Research Randomizer tool (freely available at http://www.randomizer.org/) [32]. The research assistant will use the random table to decide the group allocation of a newly enrolled participant and will inform the relevant therapist to carry out the respective intervention. The intervention therapist will not know the group allocation until the pretest measurement is completed. Each intervention group will consist of three to five participants and will be guided by a trained therapist. The participants will engage in 90 min of training, two to three times a week, for a total of 36 training sessions.

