This study is distinctive for comparing the treatment effects of various dose-matched interventions in older adults with MCI. Schaefer and Schumacher emphasized the importance of equal treatment time when designing a randomized controlled trial for older individuals with MCI [59]. This study has, therefore, designed a comprehensive assessment and intervention protocol to investigate the treatment effects of different combined therapies in people with MCI.

One big challenge that we may encounter for the study is the difficulty in recruiting participants and another is the ability to maintain those participants. Recruiting older adults who have some cognitive impairment, but do not have other neurologic or psychological disorders, could be very challenging. Those older individuals typically stay in their home community and maintain a fairly active life before they become too old to carry out household tasks. To address this problem, we will target older adults who are sent to community day care centers and some nursing homes that admit older individuals without caregivers. Furthermore, the older adults who agree to participate in the study may decide to discontinue from the program during the 36 training sessions. Dropping out of the intervention program may be due to personal reasons (e.g., falls, diseases, or low motivation) or family issues (e.g., moving, need to take care of their partner, or change in caregivers) that may prohibit them from continuing the study. We accounted for the dropout rate in the sample size estimation to ensure that we could reach sufficient power for the study.

The overall goal of this study is to compare the treatment effects of different combinations of physical exercise and cognitive training. The results of this study will be important for clinicians as well as family caregivers to select the most efficient and effective training approach to improve cognitive, physical, and daily functions in older individuals with MCI. Most importantly, the ultimate goal of these interventions is to enhance their ability to live independently and to improve their quality of life.

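### Intention-to-treat is named as the way to handle missing data, but it fills no gaps, and the repeated measures ANOVA beside it excludes anyone missing an analysed visit unless values are first imputed by a method that is not named

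*Protocol article*

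**What the plan says.** The Data analysis section names the model, "Repeated measures ANOVA will be used to determine the intervention effects for the four groups", and the software, "Data analysis will be performed with PASW Statistics 18.0 software". Its only sentence on incomplete data is "Intention-to-treat will be used for missing data". Nowhere does the article name an imputation rule, a carry-forward rule or a mixed model.

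Under Study design and procedures the trial is a "randomized controlled trial with pretest, posttest, and 6-month follow-up assessments", so each participant has up to three values per outcome.

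The Sample size estimation section expects loss: "The dropout rate in our pilot trial was approximately 20 % during the intervention period". It judges that "recruiting 16 participants for each group should be sufficient for this proposed study" and raises this to 20 per group, 80 in total, to allow for that loss. The Discussion adds that "the older adults who agree to participate in the study may decide to discontinue from the program during the 36 training sessions", and gives falls, illness, poor motivation and family circumstances as possible reasons.

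**The concern.** Intention-to-treat is a rule about the analysis set: every randomised participant counts, in the arm assigned. It does not say what to do when a MoCA or Stroop result was never obtained. The sentence therefore assigns it a task that it cannot perform.

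The method beside it makes this matter. Classical repeated measures ANOVA works on complete rows and deletes a participant who lacks any visit in the model. This is a general property of the method; the article does not state it. Taken with nothing added, the named methods would leave dropouts out of the primary-outcome analysis while the text claims intention-to-treat. The alternative is some imputation that the text does not identify. These are materially different analyses, and the wording allows the choice to be made after the data are seen.

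At stake are the loss of observed data and possible bias. Falls, illness and poor motivation may be related to physical and cognitive outcomes, so those who remain may not represent those who were randomised.

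**Working it through.** **Inputs from the protocol article**
- Per-group sizes from the three source studies: 5, 12 and 32 (Sample size estimation).
- Per-group size judged sufficient: 16 (same section).
- Dropout during the intervention: about 20% (same section).
- Randomised: 20 per group, four groups, 80 in total.
- Assessments: pretest, posttest, 6 months.

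**Assumptions, not in the article**
- Those who drop out of training also miss the posttest and the follow-up.
- Further loss between posttest and 6 months is 0%, 10% or 20% of those still in the study.
- No values are imputed before the ANOVA.

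**Step 1: reproduce the plan's own figure.**
Mean of the three sizes: (5 + 12 + 32) / 3 = 16.33, stated as 16.
Inflation: 16 / (1 − 0.20) = 20 per group; 20 × 4 = 80. This matches the plan. The inflation is sized so that 16 per group are left after dropout.

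**Step 2: complete cases for pretest and posttest.**
80 × (1 − 0.20) = 64, or 16 per group. Sixteen randomised participants (20%) are left out.

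**Step 3: complete cases if all three visits enter one model.**
Complete cases = 80 × (1 − 0.20) × (1 − further loss).

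| Further loss by 6 months (assumed) | Complete cases | Per group | Excluded of 80 |
|---|---|---|---|
| 0% | 64.0 | 16.0 | 16.0 (20%) |
| 10% | 57.6 | 14.4 | 22.4 (28%) |
| 20% | 51.2 | 12.8 | 28.8 (36%) |

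**Step 4: compare with the allowance.** The 20% is tied to the intervention period. It covers the loss of numbers in Step 2 exactly. Any later loss takes a three-visit analysis below the planned 16 per group.

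**Step 5: check that a replacement model retains the dropouts.** A mixed model with posttest and 6 months as outcomes and pretest only as a covariate has no outcome row for someone without a post-baseline visit, so the 16 in Step 2 would still be lost. With the pretest also modelled as an outcome, every randomised participant with a pretest contributes, up to all 80.

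**The case against.** The best defence is that the authors meant dropouts to be kept, with values filled in first, and used intention-to-treat as shorthand. Imputation followed by ANOVA is coherent, and an article may leave the details to a fuller document. This stands in part: a reader might infer that the plan is certainly a completers' analysis or that its two sentences flatly contradict each other, and the text does not establish either. Exclusion follows only if nothing is imputed. The defence does not rescue the sentence, though. The article does not stay silent; it fixes a rule, and the rule cannot do what is asked of it. Had carry-forward been meant, it would hold scores constant in a population for which the Background gives 10 to 15% yearly progression to dementia.

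Other stronger readings are also tempting and unsupported:
- **A participant with a posttest but no follow-up is lost even from the posttest comparison.** This assumes one model across all visits. The article does not say which visits enter; separate pretest-posttest and pretest-follow-up models fit its words equally well.
- **The combined-training arms will lose more participants.** The Discussion mentions excessive stress only as a hypothesis prompted by an earlier trial's result, and it concerns less favourable outcomes, not dropout. No figure shows differential loss.
- **The posttest comparison falls short of its planned numbers.** That loss is already covered by the increase from 16 to 20.
- **Stopping training means no assessment.** The article does not say so.

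**Conclusion.** The point holds in a conditional form. Intention-to-treat cannot serve as a missing-data method, and the named ANOVA honours it only if values are imputed by a rule that the article does not give. Without imputation, and if those who drop out also miss assessment, 64 of 80 are analysed at posttest. If in addition all three visits share one model, about 51 to 64 are analysed, the lower figure resting on an assumed 20% further loss. Any loss of numbers by 6 months is outside the plan's allowance. Bias is plausible from the stated reasons for dropout, but its direction and any difference between arms cannot be read from the document. The matter concerns the primary-outcome analysis and should be settled before the data are analysed. The Trial status section reports 39 recruited and 12 with the 6-month test completed, so there is still time.

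**What to change.** Replace the ANOVA sentence and the missing-data sentence with wording to this effect:

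*All randomised participants are analysed in their assigned group by a likelihood-based linear mixed model with pretest, posttest and 6-month values as outcomes. The model includes group, visit and group-by-visit terms, with pretest means constrained to be equal across groups. All available data are used. Participants who stop training are still invited to the posttest and the 6-month follow-up. A sensitivity analysis examines dropout related to outcome.*

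The pretest must be an outcome and not only a covariate, for the reason in Step 5. A participant with only a pretest adds little directly to the group comparison. The model also relies on missingness being explained by the observed data. Continued assessment and the sensitivity analysis are therefore both needed. Since the posttest is placed after 36 sessions, the text should also say when it falls for someone who stops earlier.

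The cost is a change of wording, slightly more analysis work and continued invitations to visits already planned. The Data management and monitoring section already gives the route for revisions, through the Institutional Review Board and the registry.
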